### Withdrawal from trial

All participants will be followed after their surgery and measured. Every attempt will be made to accommodate individual requirements to facilitate attendance at follow-up time points beyond discharge from hospital (i.e., taxi vouchers, flexible dates, appointment times). Participants will be withdrawn if they withdraw their consent, and this will be reported. Data collected until this time will be included.

### Data collection

Demographic data as well as pre-, intra- and post-operative variables will be collected as listed in Table 2. Data will be collected from the participants and their medical records. All baseline assessments will be performed at the same time of day (08:00–17.00) for each participant in the post-operative period at day 4 (±1 day) in the in-patient setting across centres to minimise potential bias in recruiting participants. The follow-up, outpatient testing at 4 weeks (±14 days) and 3 months (±14 days) will take place in the research room at RMH (Fig. 2). An independent and trained assessor (located off-site) who is blinded to allocation will conduct all measurement sessions. All tests and questionnaires will be administered face-to-face by the outcome assessors and carried out at 4 weeks and 3 months post-operatively to ensure consistency across participants. Post-hospital discharge follow-up will be conducted via phone. If participants are unable to be contacted by phone for a period of 14 consecutive days from the assessment due date, they will be considered lost to follow-up for purposes of post-discharge outcome measurement.

**Table 2 Tab2:** Data collection details

Demographic data • Name and contact details • Date of birth • Sex • Marital status • Height and weight • Occupation status • Education status • Smoking history • Past medical history and comorbidity index (Charlson comorbidity index) • Functional history (including pre-morbid functional level, use of gait aids, dominant upper limb) • Date of admission to and discharge from acute setting	
Pre-, intra- and post-operative variables • Date of cardiac surgery • Clinical information (left ventricular function, Canadian Cardiovascular Society functional classification, co-morbidities, graft type) • Type of cardiac surgery (including whether it was an emergency or elective procedure) • Other intra-operative details (including method of sternal closure, cardiopulmonary bypass time, operation time, adverse events) • Date of admission to and discharge from intensive care unit post-operatively • Risk factors for pre-, intra- and post-operative (i.e., duration of mechanical ventilation) • Type and use of pain medication (pre- and post-operatively) • Type and use of other medications (pre- and post-operatively) • Date of admission to and discharge from acute physiotherapy services • Details of physiotherapy treatment (including exercises and education provided) • Other adverse events during hospital admission (pre- and post-operatively leading to increase in length of stay); this includes superficial sternal infection, deep sternal infection, re-wiring, re-operation, pneumonia as defined in the Australian Society of Cardiac and Thoracic Surgeons (ASCTS) data • Date of readmission

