### Intervention group

The modified sternal precautions will be delivered in both verbal and written formats by the treating physiotherapists as single individualised sessions for 15 minutes on the ward prior to discharge from the hospital. Patients will be instructed to adhere to the sternal precautions for the first 4–6 weeks post-operatively (Fig. 1b).

Participants in the intervention group will be specifically encouraged to do the following:Use pain and discomfort to guide the safe use of the armsAvoid pushing or pulling with one armUse both arms close to the body during liftingUse of arms is possible, but keep them close to the bodyAvoid stretching one or both arms backwards at the same timeUse a cushion or perform sternal preservation technique (crossing the arms in a ‘self-hugging’ posture) when coughing (same as above)When transferring, roll onto the side, ease the legs over the edge of the bed and carefully use the arms to sit up from a lying position

Pain and discomfort should be used to guide the safe limits of movement. The intervention pertaining to sternal management, including the type of sternal precautions, will be delivered in both verbal and written formats to each participant separately with a flyer developed specifically for the study to ensure standardisation. In both groups, all other aspects of patient care, including pre-operative management, general anaesthesia, intra-operative ventilation parameters, fluid delivery, prophylactic antibiotic prescription, pain management, use of lines and drains, general nursing care and discharge planning, will be provided at the discretion of nurses and physicians according to routine clinical practice at both hospitals.

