### Intervention fidelity

Training will be provided for the two unblinded, dedicated staff to conduct the follow-up phone calls to ensure consistency in evaluating adherence to sternal precaution guidelines for the first 6 weeks after cardiac surgery. One staff member will evaluate the intervention group and another will follow the standard care group for both institutions. To minimise bias, the staff are required to encourage patients to continue with their allocated sternal management strategy using the standardised written instructions in addition to participants’ flyers. Participants will be informed that they will be contacted via telephone weekly to help reinforce their exercise and precaution guidelines for the first 6 weeks after cardiac surgery. Specifically, the standard care participants will be asked to follow the restriction on the use of their upper limbs and to limit the activities of their upper limbs and trunk during activities of daily living, bed transfers, and sit-to-stand manoeuvers. The intervention group will be encouraged to use their upper limbs bilaterally to perform activities of daily living, bed transfers and sit-to-stand manoeuvers. They will also be encouraged to perform upper limb exercise three times daily within the limits of pain and discomfort.

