### Statistical methods

Statistical analyses will be performed by the biostatistician. All data will be analysed using the intention-to-treat principle. Descriptive statistics, including mean and SD, median and interquartile range, number and percent, and frequency will be used to summarise data (depending on distribution and type of data). This also includes participant demographics and adherence to sternal precautions. A comparison between the two hospitals will be conducted on the demographic profile of the participants to establish differences in each presenting population.

The primary outcome—the change from baseline to 4 weeks in the SPPB—will be analysed using a mixed between-and-within subjects analysis of variance with repeated measures across participants. The primary hypothesis will be examined by a contrast evaluating change from baseline to the 4-week time point in the modified sternal precaution group compared with the standard care group. The analysis will be carried out according to the intention-to-treat principle, based on the groups to which participants were randomised. The interactions between group and time will be examined first to assess the effect of intervention, and, if no interaction is present, then group and time main effects will be examined. If there are issues with non-normality or ceiling/floor effects of the SPPB, transformation or dichotomisation will be considered. If there are participants who are not following the assigned group protocol, we will consider a supplementary per-protocol analysis. Key secondary outcome data (including upper limb function, pain, kinesiophobia and HRQoL) will be summarised and analysed similarly to the primary outcome.

Logistic regression will be used to determine pre-, peri- and post-operative risk factors associated with the development of post-sternotomy complications. This will be an exploratory analysis which may identify trends of predictors reported in the literature having an individual effect on post-operative sternal complications (i.e., female sex, diabetes mellitus, obesity, bilateral internal mammary artery grafts, re-operation for post-operative complications, and blood product requirement were reported as significant predictors of sternal infection). For all tests conducted, a *p* value <0.05 (two-tailed) will be considered statistically significant, and mean differences (95% confidence intervals) will be reported.

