Previous studies have shown that unsupported, frequent coughing is the single main cause of mechanical stress through the sternum and may be a far more significant factor in the development of sternal complications [17, 19]. Further, recent evidence demonstrated that upper limbs and trunk movement cause minimal micromotion of the sternal edges (<2 mm) as measured by real-time ultrasound [17]. Therefore, it was proposed that strict post-operative movement restrictions may not be necessary for all patients [8, 13]. However, upper limb movements are part of post-operative standard physiotherapy treatment. In some institutions, this represents instructions on ‘no use of the arms’, or limiting the use of the arms to 90-degree elevation for varying periods of time [8, 13, 14, 25]. Concurrently, patients are encouraged to perform active movements of the upper limbs as part of their post-operative care following cardiac surgery with the aim of restoring physical function [8]. This creates a clinical dilemma collectively for both health professionals and patients [8, 13]. On the basis of findings of a recent survey conducted in Australia [13], we have chosen to modify sternal precaution guidelines encouraging the use of bilateral upper limbs and trunk activities with pain and discomfort as a safety guide in the intervention group to optimise sternal healing and functional recovery in this patient population. Specifically, participants will be allowed to resume their normal load-bearing activities at their own pace within pain-free limits by keeping their upper arms close to their body for common activities (e.g., getting out of bed, lifting and transferring). We hypothesise that this intervention will be safe and cause no harm to the participants. In addition, prior research suggests that unloaded movements within a pain-free range and loaded activity with the upper arms close to the body will not cause excessive stress on the sternal surgical site or bone [8, 19, 62, 65].

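### Table 2 records sternal infection, re-wiring and re-operation only as in-hospital events that lengthen stay, while the allocated precautions are followed mainly at home, so the no-harm hypothesis and the complications regression are only partly covered

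*Protocol article*

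**What the plan says.** - **Which harms are recorded, and when.** Table 2 (Data collection) has the item "Other adverse events during hospital admission (pre- and post-operatively leading to increase in length of stay" and specifies that "this includes superficial sternal infection, deep sternal infection, re-wiring, re-operation, pneumonia as defined in the Australian Society of Cardiac and Thoracic Surgeons (ASCTS) data". This sets both a window (the admission) and a filter (a longer stay).
- **When the intervention acts.** Baseline testing is on post-operative day 4 (±1 day) (Data collection), and allocation follows it (Randomisation and allocation). The precautions are given in "single individualised sessions for 15 minutes on the ward prior to discharge from the hospital", and then "Patients will be instructed to adhere to the sternal precautions for the first 4–6 weeks post-operatively" (Intervention group). The control group section has the same session and the same period.
- **What reaches past discharge.** Table 2 lists "Date of readmission" with no cause. The modified Sternal Instability Scale (SIS) is a secondary outcome, and Data collection puts all tests at 4 weeks and 3 months with a blinded assessor. The data and safety monitoring committee reviews serious adverse events (Data management and quality). Participants are "contacted via telephone weekly to help reinforce their exercise and precaution guidelines for the first 6 weeks after cardiac surgery" (Intervention fidelity).
- **What relies on these data.** The Discussion states: "We hypothesise that this intervention will be safe and cause no harm to the participants". Statistical methods states: "Logistic regression will be used to determine pre-, peri- and post-operative risk factors associated with the development of post-sternotomy complications".

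**The concern.** The precautions exist to prevent sternal complications, and the trial relaxes them. The harms of interest are those that arise while patients follow the allocated advice, which is mostly at home. For infection, re-wiring and re-operation, the stated item stops at discharge. A wound infection that first appears at home cannot occur during the index admission or prolong it. Conversely, some events inside the window will precede allocation and cannot be effects of it.

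Followed as written, the item would miss most events that could bear on the no-harm hypothesis. It would also give the exploratory regression an outcome cut off at discharge for every complication except instability. A low or equal count from that item could then be reported as reassurance that it does not provide.

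**Working it through.** **1. The article's own sample size.** The only sample size given is for the Short Physical Performance Battery (SPPB): difference 2, SD 2.7, two-sided alpha 0.05, power 0.80. Per group, n = 2 × (1.96 + 0.84)² × (2.7/2)² ≈ 28.6, so 29, or 58 in total, as stated. Allowing for 20% dropout, 58/0.8 = 72.5, against the stated 72. No rate, margin or power is given for sternal complications.

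**2. Share of the exposure period inside the Table 2 window.** Randomisation is at about day 4 and the precautions run to at most day 42, which leaves 42 − 4 = 38 days. The article gives no discharge day, so it is assumed:
- discharge on day 6: (6 − 4)/38 = 5%
- discharge on day 8: (8 − 4)/38 = 11%
- discharge on day 10: (10 − 4)/38 = 16%

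With a 4-week period (28 − 4 = 24 days), discharge on day 6–8 gives 2/24 = 8% to 4/24 = 17%. These are shares of days. They equal shares of complications only if risk is constant over time, which the article does not say. Trial design places baseline testing in an outpatient setting. I used the in-patient timing in Data collection, which fits teaching before discharge.

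**3. Coverage by type of event after discharge.**
- Instability or separation: covered by the SIS. The 4-week and 3-month timing is inferred from the general sentence on all tests, because the schedule figure is not shown.
- Superficial infection treated without readmission: no itemised collection.
- Deep infection, re-wiring, re-operation: reached only through a readmission date without cause, or through serious adverse event review with no stated collection window.
- Telephone contacts: the weekly calls are described only for adherence and reinforcement. Data collection also mentions telephone follow-up after discharge without saying that it records complications.

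**4. What full capture would yield.** The Background cites a complication rate of 0.4% to 8%.
- Expected events per arm of 36: 36 × 0.004 = 0.14 to 36 × 0.08 = 2.9.
- Expected events in all 72: 0.29 to 5.8.
- Zero events in 36: one-sided 95% upper limit 1 − 0.05^(1/36) = 8.0%, the top of the cited range. With 29 evaluable, 1 − 0.05^(1/29) = 9.8%.
- Illustration, assuming a doubling from 8% to 16%: power of Fisher's exact test at 36 per arm is about 9%, and about 258 per arm would be needed for 80% power (normal approximation).

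**The case against.** The strongest reply is that the article does look past discharge. The Background counts instability among the sternal complications. The SIS measures it in both arms with a blinded assessor, and its top score describes a completely separated sternum. Review of serious adverse events carries no in-hospital limit, and data come from participants and their records, so the cause of a readmission could be retrieved. The article is also condensed: the schedule figure and full protocol are not shown, and either may contain a post-discharge adverse event procedure.

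Much of this stands, and it rules out three stronger readings that a reader might infer.
- **That sternal complications are collected only in hospital.** The SIS, the readmission date and the committee review contradict this.
- **That the Table 2 window is what makes the safety hypothesis untestable.** With 36 per arm, even full capture would support only description. The trial is powered on the SPPB, and safety is not among the stated aims.
- **That a finding of no difference is built in.** Statistical methods plans no between-arm test of complications, and the regression is an exploratory analysis of risk factors.

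The reply does not remove the narrower point. Table 2 is not silent: it states a window and a filter for named sternal harms, and both fit the exposure period poorly. The SIS does not record infection, re-wiring or re-operation. A superficial infection may not count as serious, and the committee's charter had yet to be written. With so few events expected, each one lost after discharge matters more.

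**Conclusion.** The point holds for infection, re-wiring and re-operation. Their only itemised collection is confined to the admission and to events that prolong it, which is about 5–11% of the days from randomisation to 6 weeks if discharge is on day 6–8. Instability or separation is covered at follow-up, provided the SIS is done at both visits. The no-harm hypothesis and the complications regression are therefore partly covered.

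Sample size is a separate limit. At 0.14–2.9 expected events per arm, and an 8.0% upper limit with none observed, the trial can describe safety but cannot establish it. The conclusion rests on the assumed discharge day and on the article as shown. A post-discharge procedure in the full protocol would reduce the point to a correction of Table 2.

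**What to change.** - **Redefine the Table 2 item** as sternal complications (superficial and deep infection, dehiscence or instability, re-wiring, re-operation, and readmission with its cause) from randomisation to the 3-month visit, whatever the effect on length of stay. List events before randomisation separately.
- **Ascertain them the same way in both arms**, at the blinded 4-week and 3-month visits and from medical and readmission records. The weekly calls should not be the source, because an unblinded caller follows each arm and the caller differs between arms. A call can at most prompt a check of records.
- **Report counts by arm with exact confidence intervals**, and state that 36 per arm can describe safety but not establish it.
- **Cost.** A few fields at existing visits. Since follow-up is complete, in practice this means record retrieval for 72 patients at two adjacent hospitals and one table by arm. Where records cannot be retrieved, the report should state the capture window used and limit its safety statement accordingly.

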**Fig. 2 Fig2:**
[figure not shown]
Standard Protocol Items: Recommendations for Interventional Trials (SPIRIT) checklist for the schedule of enrolment, interventions and assessments

### Outcomes assessment

#### Primary outcome: Short Physical Performance Battery

The Short Physical Performance Battery (SPPB) is a functional test that measures daily functional activities in the acute care in-patient older population, including cardiac surgery [26]. The test is a well-established and validated measure of lower extremity performance and is designed to simulate routine physical activities in older adults [27]. The test includes gait speed (8-foot walk), standing balance, and lower extremity strength and endurance (chair rise task). It is comprised of the following:
*Gait speed:* Participants will be instructed to walk a distance of 8 feet as determined by traffic cones on a flat surface at their normal, comfortable pace. The average of two trials will be used. For safety reasons, participants are encouraged to walk with their gait aids if these are usually used or are part of their post-operative care at the time of testing. An 8-foot course was used, and scoring will use the faster of the two walk times to calculate speed in metres/second. A reduction of the distance to measure gait speed has been shown to provide valid data in measuring of functional limitations [28, 29].
*Standing balance:* Participants will be assessed in three different static positions (side-by-side stand, semi-tandem stand and tandem stand). Participants will be instructed to try to hold each of these positions for 10 seconds.
*Chair rise task:* Participants will be instructed to stand up and sit down five times in a row as quickly as possible.

The SPPB score is based on timed measures of standing balance, walking speed and ability to rise from a chair. Each test is scored on a scale of 0 to 4 points, with a summary performance score range of 0–12 points using cut-point criteria established by Guralnik et al. [27]. A 0 score indicates poor function, whilst 12 indicates excellent function. If the participant is unable to perform a specific test, a score of 0 will be assigned. A score of 10 or lower is considered the cut-point for mobility impairment [27]. The SPPB was selected because it assesses overall functional performance that reflects physical function required to perform everyday tasks. It is hypothesised that the intervention will impact overall functional performance because this is the primary concern of most patients at medium- to long-term follow-up (6 weeks to 12 months) [26, 30]. The test has established validity and reliability in measuring physical performance in the elderly [27, 31, 32] with an intra-class correlation coefficient (ICC) equal to 0.82 [32], and it is a strong predictor of disability in non-disabled older persons [33]. The minimal detectable change values range from 0.54 [34] to 2 points [35], which suggests that a change in physical performance of 1 to 2 points is a clinically meaningful change in an older [34] and in-patient stable cardiovascular population [35]. Therefore, in the absence of data for cardiac surgery populations, the minimal important difference (MID) for this study was derived from prior research with a cohort of patients with stable cardiovascular conditions of 2 points, which is representative of our participant population. The SPPB has been shown to be reliable, valid and sensitive to change [36]. ICCs ranged from 0.88 to 0.92 for measures done 1 week apart, with a 6-month average ICC of 0.78 [36].

#### Secondary outcomes

*Functional Difficulties Questionnaire (FDQ):* The FDQ measures the functional status of patients following cardiac surgery, with a particular focus on upper limb and trunk function in patients following a median sternotomy [37]. The questionnaire requires patients to rate the difficulty they would experience when completing a series of 13 upper limb and trunk functional tasks. Specifically, patients are asked to place a mark along a 10-cm line, with anchors indicating ‘no difficulty’ and ‘maximum difficulty’ on the left and right sides of the line, respectively. For those activities that participants cannot complete while filling out the questionnaire, they will be asked to recall the last time they performed the tasks. The 13 functional tasks included in the questionnaire are everyday tasks that were nominated as difficult to perform in a pilot study of patients following cardiac surgery [37]. Previous research has demonstrated that the FDQ is a valid, reliable and responsive measure in this patient population with minimal recall bias, and it has been used to measure the functional status of patients following cardiac surgery in both the short term (4 weeks post-operatively) and long term (3 months post-operatively) [37]. The follow-up time points are a minimum of 4 weeks to 2 months apart, thus further reducing recall bias.
*Patient-identified cardiac pain using numeric and visual prompts:* This is a pain outcome measurement tool that was developed by Teoh et al. [38]. To obtain data regarding symptom presentation, participants are required to identify on a gender-neutral silhouette torso all locations of their pain or discomfort. The participants are also required to identify their ‘chief’ or ‘main’ symptom, describe its nature by pointing to pictorial identifiers that visually represent a description of the pain (i.e., stabbing, heavy, shooting, burning, squeezing) [39]. The intensity of the pain forms the last domain and uses a Likert-type scale. This tool was selected because it evaluates multiple dimensions of pain and discomfort, is easy to administer and accounts for cultural diversity [40].
*Short Form McGill Pain Questionnaire 2 (SF-MPQ-2):* Pain quality will be measured using the SF-MPQ-2, which consists of 22 items investigating 4 dimensions of pain quality (continuous, intermittent, neuropathic and affective) on an 11-point numerical rating scale [41]. The total score is calculated from the mean of 22 items, and scores for the 4 dimension subscales are calculated from the mean of the items included in each subscale. Scores on each subscale can range from 0 to 10. A higher score indicates more severe pain [41]. Participants will be instructed to choose the number that best describes their intensity of pain and related symptoms experienced during the past week. A 0 score will be assigned if the word does not describe the participant’s pain or related symptoms. The original version of the scale (SF-MPQ) has well-established reliability in cardiac populations with α coefficients ranging from 0.75 to 0.83 across various post-operative days [42, 43]. The SF-MPQ-2 is sensitive to change in chronic pain, and total and subscale scores are responsive to change. The changes are associated with patient ratings of global improvement in clinical trials [41].
*Tampa Scale of Kinesiophobia shortened version (TSK-11):* The TSK-11 is a widely used tool to measure pain-related fear beliefs about movement and re-injury [44]. It is an adaptation of the original 17-item instrument [44] designed to assess fear of movement or re-injury that excludes the 4 original reverse-scored items that were found to have small item-to-total score correlations. The adapted score is an 11-item instrument where respondents will be asked to rate each item on a 4-point Likert scale, ranging from 1 (strongly disagree) to 4 (strongly agree). The TSK-11 is a reliable and valid measure of fear of movement or re-injury in patients with chronic pain [45, 46]. It has internal consistency, reliability and convergent validity with a Cronbach’s α of 0.80 for the total score [46]. A reduction of at least 4 points on the measure maximises the likelihood of correctly identifying an important reduction in fear of movement [46].
*Grip strength:* Hand-grip strength will be measured in kilograms with a hand-held Jamar dynamometer (Performance Health, Warrenville, IL, USA). The participant will be tested in the position recommended [47]. The peak value of the maximal squeeze over 5 seconds will be recorded [48]. Time intervals were allowed between tests. A previous study showed similar test-retest reliability with one trial alone, a mean of two or three trials and a maximum of three trials [49]. In addition, because of influences of pain after surgery, the average may not reflect true performance. Therefore, in this study, three serial tests of maximum grip strength with the dominant hand will be performed, and best of the three values will be recorded. Hand-held dynamometry is a reliable, objective tool for muscle strength measurement [50] and a predictor of post-operative complications, mortality and functional decline [51]. The test is a reliable and responsive measure for patients in cardiac rehabilitation (ICC 0.97 for right and left hand grip strength) [52].
*Medical Outcomes Study 36-item Short Form Health Survey (SF-36v2):* HRQoL will be evaluated by SF-36v2, which is a generic measure to assess eight domains, including physical functioning, role physical functioning, role emotional functioning, mental health, vitality, social functioning, bodily pain and general health. All scale or single-item measurements range in score from 0 to 100 and will be administered by interview. The raw sub-scale scores will be transformed to ‘norm-based’ scores using published algorithms [53]. Norm-based physical and mental component summary scores will be calculated from raw sub-scale scores, with higher scores indicating better quality of life. A higher score on the SF-36v2 sub-domains represents a high level of functioning and higher quality of life [54]. The scale has good reliability, with Cronbach’s α values ranging from 0.65 to 0.96 for all subscales [54]. The instrument can differentiate between levels of health among post-CABG individuals at a single time point and over time [55]. Furthermore, the SF-36v2 is valid in written format as well as verbal administration over the telephone in cardiac patients [56].
*Modified Sternal Instability Scale (SIS):* The modified SIS will be used to assess sternal instability. It is a manual test that measures the stability of the sternum on a 4-point scale (0–3)﻿. A score of 0 corresponds to a clinically stable sternum with no detectable motion or separation of the sternal edges, whilst a score of 3 corresponds to a completely separated sternum with marked increased motion or separation of the sternal edges﻿. The original 5-point (0–4) SIS is a valid and reliable clinical tool for measuring the stability of the sternum in patients following a median sternotomy [8, 57]. It has excellent inter- and intra-rater reliability, with ICCs of 0.97 and 0.98, respectively [58].
*Adherence monitoring:* A questionnaire was developed by the researchers to monitor the level of adherence of all patients following cardiac surgery via median sternotomy. The list of activities, duration of adherence and rate of adherence are rated on a numeric scale. Participants are prompted to complete the questionnaire by telephone on a weekly basis. They are additionally encouraged to follow the guidelines on sternal management as per their specific flyers. An adherence threshold for the experimental group was set at a participant self-perceived reported rating ≥70%.

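### The SF-MPQ-2 past-week recall at a day 3 to 5 baseline reaches back across the operation, so change from baseline cannot be read as resolution of post-sternotomy pain

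*Protocol article*

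**What the plan says.** Under Secondary outcomes, the SF-MPQ-2 is scored as the mean of 22 items rated 0 to 10, and the recall period is the week before the assessment: participants are to "choose the number that best describes their intensity of pain and related symptoms experienced during the past week". No other recall period is given for the first visit.

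Under Data collection, all baseline assessments are done "in the post-operative period at day 4 (±1 day) in the in-patient setting", and follow-up is "outpatient testing at 4 weeks (±14 days) and 3 months (±14 days").

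Under Statistical methods, the primary hypothesis is tested by a "contrast evaluating change from baseline to the 4-week time point in the modified sternal precaution group compared with the standard care group". The interaction of group and time is looked at first. If there is none, the main effects of group and of time are looked at. On the secondary outcomes the section says: "Key secondary outcome data (including upper limb function, pain, kinesiophobia and HRQoL) will be summarised and analysed similarly to the primary outcome". Table 1 lists the SF-MPQ-2 among the key secondary outcomes, and the trial objective names sternal pain and discomfort at 4 weeks and 3 months.

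**The concern.** A change score needs the same quantity at both ends. At 4 weeks and 3 months the past week describes pain after the sternotomy. On day 3, 4 or 5 it covers the post-operative days and some days before the operation. Those earlier days may have been free of pain or, since patients having coronary bypass surgery are eligible, may have included cardiac pain. The mix also depends on which day the patient is assessed.

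At stake is the interpretation of a key secondary outcome. If a fall in SF-MPQ-2 score, or a significant time effect, is reported as resolution of post-sternotomy pain, the baseline may not be the post-operative starting point that this reading assumes.

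**Working it through.** The article gives no numerical assumption for the SF-MPQ-2, so there is no planned figure to reproduce for it. The 29 per group used below is the evaluable number under Sample size, and it does reproduce: 2 × (1.96 + 0.84)² × 2.7² / 2² = 28.6, rounded up to 29.

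**1. Pre-operative part of the window.** Inputs: a 7-day recall and assessment on post-operative day d = 3, 4 or 5.

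| Day d | Elapsed days, 7 − d | Share of the week | Strict calendar count, 6 − d | Share of the week |
|---|---|---|---|---|
| 3 | 4 | 57% | 3 | 43% |
| 4 | 3 | 43% | 2 | 29% |
| 5 | 2 | 29% | 1 | 14% |

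The strict count includes the assessment day in the week and does not count the day of surgery as pre-operative. On either count, every permitted baseline day reaches back before surgery. The earliest 4-week visit is day 28 − 14 = 14, so its window contains no pre-operative day.

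**2. Possible effect on the baseline score.** The pain levels here are assumed, because the article gives none. The answer is also assumed to average evenly over the week. Recorded baseline = [(7 − d) × pre + d × post] / 7. With post-operative pain 4:

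| Pre-operative pain | Day 3 | Day 4 | Day 5 |
|---|---|---|---|
| 0 | 1.71 | 2.29 | 2.86 |
| 1 | 2.29 | 2.71 | 3.14 |
| 2 | 2.86 | 3.14 | 3.43 |
| 4 | 4.00 | 4.00 | 4.00 |

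If pain was the same before and after surgery, nothing is lost. If patients rate only the days since surgery, nothing is lost either.

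**3. Effect on the mean change.** Assume post-operative pain P with mean 3 and SD 1.5, pre-operative pain with mean 1 and SD 0.5 or 1.0, follow-up = 1 + 0.5 × (P − 3) + error with SD 1.2, and days 3, 4 and 5 equally likely. The average pre-operative share is 3/7, so the recorded baseline averages (3/7) × 1 + (4/7) × 3 = 2.14. The mean change is 1 − 2.14 = −1.14, against 1 − 3 = −2.00 for post-operative pain alone.

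**4. Effect on the precision of the change contrast.** For pre-operative share w and pre-operative SD s, the variance of change on a given day is (0.5 − w)² × 2.25 + w² × s² + 1.44.

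- No mixing (w = 0): 0.5625 + 1.44 = 2.0025, SD 1.415. SE of the between-arm contrast with 29 per arm: 1.415 × √(2/29) = 0.372.
- Mixing, averaged over the three days and with the variance of the day means (0.054) added: for s = 0.5, 0.042 + 0.049 + 1.44 + 0.054 = 1.586, SD 1.26, SE 0.331. For s = 1.0, 0.042 + 0.197 + 1.44 + 0.054 = 1.734, SD 1.32, SE 0.346.

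The correlation of baseline with follow-up falls from 0.53 to 0.49 (s = 0.5) or 0.45 (s = 1.0). The blended baseline also varies less, however, and the change contrast does not lose precision. A second model (post-operative mean 4, pre-operative mean 1.5, both with SD 1.5, true arm difference −0.5) gave SE 0.371 without mixing and 0.372 with it. The estimated arm difference stayed at about −0.50, while the mean change moved from −2.25 to −1.18.

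**5. Follow-up score adjusted for baseline, model of step 3 (simulated).** The residual SD is 1.20 without mixing. With mixing it is 1.24 (s = 0.5) or 1.26 (s = 1.0) after adjustment for the baseline score, and 1.22 or 1.25 with assessment day added. The SD of change under mixing is 1.26 or 1.32, so adjustment is about 3 to 5% better on the SD scale.

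**The case against.** The trial's question is comparative. Baseline testing comes before the envelope is opened (Randomisation and allocation), so any blending is the same in expectation in both arms and cancels from the contrast. The stated aim is pain under modified against standard precautions at 4 weeks and 3 months, not how fast pain resolves within an arm. This stands in full. A reader might infer from the weaker baseline correlation that the change contrast is biased or less precise. Neither follows: the arms are affected alike, and in the models above the SE falls or does not move.

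The size rests on invented pain levels and on even averaging over seven days. The instruction asks for the number that best describes the pain, and a patient a few days after sternotomy may well answer about surgical pain. This also stands: the dilution could be close to nil.

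Baseline use of the SF-MPQ-2 is inferred, since the assessment schedule is a figure that is not shown, and the form may carry its own wording. The inference is strong, because an analysis of change cannot be run without a baseline score, but it remains an inference. In addition, Trial design places baseline testing in an outpatient setting and Data collection places it on the ward; only Data collection gives the day.

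What the objection does not remove is the mismatch in the text, or the provision to examine a time main effect when there is no interaction. The time effect is the quantity that the mismatch touches.

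**Conclusion.** The point holds as one of interpretation for a secondary outcome. Read literally, the baseline week contains roughly 1 to 4 pre-operative days (14% to 57% of the window) and the follow-up weeks contain none. This clouds the baseline score, the within-arm change and the time main effect. Where pain before surgery was lower than after it, the recorded fall is too small; with marked pre-operative cardiac pain the distortion could go the other way. The amount is unknown. The movement from −2.00 to −1.14 depends wholly on the assumed pain levels and on averaging over the week.

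The documents do not support a claim of bias between arms or of a less precise change contrast, and the primary outcome is not affected. All of this assumes that the SF-MPQ-2 was given at baseline with the same past-week wording.

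**What to change.** For the SF-MPQ-2, replace the change-from-baseline contrast with a between-arm comparison of the 4-week and 3-month scores, adjusted for the baseline score and for the post-operative day of the baseline assessment. State that neither the change from baseline nor the time effect will be reported as resolution of post-sternotomy pain. If the baseline form in fact used a different recall period, say so.

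The cost is a sentence or two in the analysis plan. No new data are needed: the date of surgery is in Table 2, and the assessment day follows from it and the date of the baseline visit.

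Rewording the baseline question to cover only the time since the operation would help only if baseline data were still to be collected. Trial status reports that all follow-up was completed in April 2017. That wording would also give a recall of 3 to 5 days at baseline against 7 days at follow-up.
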